##### 8.6.4.2 Labelling of the drugs

Labelling will be done in both Chichewa and English. This will include study name, investigative institute, cluster name and study identification number of the participant, staff contact number, drug dose and usage directions and precautionary measures to be observed when taking the drug.

##### 8.6.4.3 Storage of drugs at the study clinic

The study drugs will be stored in a designated study pharmacy in a secure area with access limited to designated trial staff. Appropriate storage conditions as specified on the study drug pack will be observed.

##### 8.6.4.4 Product accountability

The investigator will be responsible for establishing a system for the correct handling of study drug to ensure that:

1. Deliveries of study drug from the sponsor are correctly received by a responsible person (e.g. pharmacist assistant)
2. Accurate records are maintained for the receipt of study drug, for the dispensing of study drug to subjects and for returned drug.
3. Certificates of delivery and return must be signed preferably by the investigator or authorised personnel and copies retained in the investigator file.
4. Study drug is to be handled and stored safely and properly and in agreement with the given storage instructions.
5. The study drug is to be prescribed only by the principal investigator, co-investigators or study site personnel authorised to do so by the principal investigator.
6. Study drug is dispensed only to study subjects in accordance with the protocol.
7. Subjects must return all unused medication and empty containers to the investigator.
8. At the end of the study delivery records must be reconciled with records of usage and returned stock. Any discrepancies must be accounted for in writing.

Once accounted for any returned and unused study treatment at the site will be returned to the sponsor for destruction or destroyed locally upon agreement with the sponsor. Drug destruction certificates will be issued that refers to the subject study numbers for subject specific medication that was destroyed.

##### 8.6.4.5 Dispensing of trial drug

Designated staff will be responsible for dispensing the drug to mothers/guardians of participants. Each time the drug is dispensed, the amount dispensed, the name of the participant, date and signature of the person dispensing the drug will be recorded in the log file.

#### 8.6.4.6 Iron and folate supplementation

All children in all the five arms, regardless of Hb level, will receive a standardized prophylactic dose of iron supplementation (about 2 mg/kg) from two weeks into the study onwards for a period of about 4 weeks (i.e. until the next dose of PMC-DP is due at 6 weeks). Iron can be given as mono-therapy or as part of the fixed-dose formulation with folic acid.

#### 8.6.5 Prohibited medications

Prohibited medication includes antimalarial drugs not prescribed within the trial protocol and other drugs with antimalarial properties.

### 8.7 SELECTION AND WITHDRAWAL OF STUDY PARTICIPANTS

#### 8.7.1 Inclusion Criteria

#### 8.7.2 Eligibility criteria for pre-study screening

Parents / guardians of children who fulfil the pre-screening eligibility criteria will be informed about the existence of the study by the hospital and/or study staff. Consent will not be obtained at the acute stage of the illness but a few days later preferably at discharge when the child has recovered and is able to switch from parenteral to oral medication (see section below). This provides a time window of 1 to 3 days for the parents or guardian to reflect on the study and discuss it with family members.

Pre-study screening will be done by hospital staff or study staff. No study specific information or samples will be collected in this pre-study screening period. The role of the study team during this period is to review the diagnosis and ensure that the potential study participants get the standard quality of care for severe malarial anaemia.

Each pre-screened subject will be assigned a pre-screening number in sequential order by the hospital regardless of whether they fulfil the pre-screening eligibility criteria. Data will be recorded on a pre-screening log that will be kept in the investigator's site file. This record will be used to report how many patients were pre-screened and how many were eventually recruited in the study to establish that the study population was selected without bias. This screening log will not contain names or other identifying information

#### 8.7.3 Screening and Consent

The parents of the children will be approached for a screening interview as soon as the child is sufficiently recovered to take oral medication (i.e. after completion of the blood transfusion and the standard parenteral artesunate medication). This is typically within 48 hours following admission to the hospital. During this interview verbal consent will be sought from the parents or guardian and if granted the eligibility criteria for inclusion in the study will be assessed.

##### 8.7.3.1 Informed Consenting process

The participant will be given the informed consent form translated in Chichewa language. In the case of an illiterate carer, the study staff will read the consent form to the prospective participant in the presence of a witness who is not part of the study. The witness will sign the consent form to attest that information in the consent form was accurately explained and that informed consent was freely given. Study staff will answer

any questions prior to asking the carer to consent. The consent form will be translated to Chichewa from English and then back translated to verify accuracy.

If a carer is illiterate, a thumbprint will be accepted as a legally effective signature. Carers will be advised that they are free to decline any question or procedure and that they may terminate their participation at any time without loss of any benefits and usual child care they receive at the hospital. Consent will be signed either with carbon copies or otherwise with two identical consent form per carer. One signed or thumb printed consent form will be kept on file by the study team and one will be given to the participant.

The consenting process will take place at the study clinic.

#### 8.7.3.2 Screening log

The investigator will keep a subject screening log for all subjects considered for enrolment regardless of whether they were enrolled, which combined with the pre-screening log will be used to establish that the study sample was selected without bias. This screening log will not contain names or other identifying information.

#### 8.7.4 Enrolment

Once the parent/guardian provides informed consent for his/her child to participate in the study, the participant will be assigned a study ID and randomised to one of the five study arms.

##### 8.7.4.1 Assignment of study IDs

Pre-screened subjects who meet all eligibility criteria will be issued a study subject number during this visit. Once issued the study subject number they will be considered as 'enrolled'. This number is the subject's unique identifier and used to identify the subject on the CRFs. Subject numbers will be assigned strictly sequentially as subjects enter the study. Once a number has been assigned no attempt will be made to use that number again, for example even if a subject discontinues or is a screening failure.

##### 8.7.4.2 Randomisation procedure at discharge

The unit of randomization will be the villages, defined as the smallest administrative unit overseen by a Village headman. A group Village headman oversees several villages. Ninety (90) villages in the catchment areas of Zomba district located in the southern region of Malawi will be involved in the study. Zomba Central Hospital participated in previous related studies [1, 15-17] and is particularly suitable for the delivery trial because of the existing linkages with community based health care providers and rural clinics within their catchment areas. A 1:1 allocation ratio will be used. To minimize imbalances across groups with respect to baseline malaria prevalence and risk factors for malaria, location-specific baseline information on malaria indicators, such as the prevalence of positive RDTs or microscopy in the 12-month period prior to the trial (Under-five registry data) will be considered in selection of villages.

Randomisation will be done by opening a single concealed envelope, which will contain the cluster and study arm.

#### 8.7.4.3 Clinical assessment:

After consent is obtained and the subject's eligibility is confirmed the subject's demographic data will be recorded in the CRF, and all relevant clinical information, including the previous and current medical history, and laboratory information copied from the hospitals clinic and laboratory notes to the CRF (see CRF for details). A further clinical examination (including anthropometrics) will be performed and a medical history taken that will serve as the baseline examination and captured on the CRF.

#### *Inclusion criteria for enrolment into pre-study screening period*

1. Haemoglobin <5.0g/dl or PCV <15%, or requirement for blood transfusion for other clinical reasons on or during admission to the hospital
2. Age between 4 months (inclusive) and 59 months (inclusive)
3. Body weight >5kgs

#### *Exclusion criteria for enrolment into pre-study screening period*

1. Recognised specific other cause of severe anaemia (e.g. trauma, haematological malignancy, known bleeding disorder, known sickle cell disease)

#### 8.7.4.4 Eligibility criteria for enrolment into study

##### *Inclusion criteria*

1. Fulfilled the pre-study screening eligibility criteria
2. Clinically stable, able to switch to oral medication,
3. Subject completed blood transfusion(s) in accordance with routine hospital practice
4. Able to feed (for breastfed children) or eat (for older children)
5. Able to sit unaided
6. Provision of informed consent by parent or guardian

##### *Exclusion criteria*

1. Previous enrolment in the present study
2. Used DHP since screening
3. Fever (>37.5 °C) on the day of randomisation
4. Known hypersensitivity to study drug
5. Child resides outside catchment area during the course of the study (6 months)
6. Known need at the time of enrolment for concomitant prohibited medication during the 14 weeks PMC treatment period
7. On-going participation into another clinical trial involving ongoing or scheduled treatment with medicinal products during the course of the study (6 months)
8. Suspected non-compliance with the follow-up schedule
9. A known need for scheduled surgery during the course of the study (6 months)
10. Suspected non-compliance with the follow-up schedule

HIV infection and cotrimoxazole prophylaxis are not exclusion criteria

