|                        | Allocation: cluster randomised; intervention model: parallel assignment; arms: 5; allocation ratio 1:1; Masking: open-label                                                                                                                                                                                                                                                                                                                                                                                                                                                                                                                                                                                                                                                                                                                                                                                                                                                                                                                                                                                                                                                             |
|                        | Primary purpose: prevention                                                                                                                                                                                                                                                                                                                                                                                                                                                                                                                                                                                                                                                                                                                                                                                                                                                                                                                                                                                                                                                                                                                                                             |

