### **7.3 OUTCOMES**

#### **7.3.1 Primary outcome**

100% of PMC drugs uptake (defined as administration of **all** 3-day treatment courses, given 2, 6 and 10 weeks after discharge) assessed by unannounced spot checks

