## 8.9 OUTCOMES

### 8.9.1 Primary Outcome

The primary outcome is the 100% of PMC drugs uptake (defined as administration of **all** 3-day treatment courses, given 2, 6 and 10 weeks after discharge) assessed by unannounced spot checks.

The PMC uptake will be assessed through a study questionnaire administered at unannounced spot checks to determine if and when children and their mothers/guardians attend the scheduled dosing of the drug. The spot checks will be conducted at day 4 or 5

of each DHP treatment course. The effectiveness of the delivery mechanism will be determined by the following measures:

1. **Pill count:** Research Assistants will perform a pill count of the drugs available at the day of the visit. This will be used to assess whether participants took the whole course of DHP or not.
2. **Interview:** A face-to-face interview with the mothers/guardians of children participating in the study will be done to collect information on missed doses and possible reasons for any missed doses.

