#### 8.12.3.3 Assignment of study IDs

Eligible subjects will be issued a study subject number during the enrolment visit. Once issued the study subject number they will be considered as 'enrolled.' This number is the subject's unique identifier and used to identify the subject on the CRFs. Subject numbers will be assigned strictly sequentially as subjects enter the study depending on the cluster the participant will be coming from. Once a number has been assigned no attempt will be made to use that number again, for example if a subject discontinues or is a screening failure. Study participants will be randomised to study arms depending on the cluster from which they come from.

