##### **11.7.2 Randomisation procedure**

The trial statistician [name] will computer-generate list of sets of matched clusters and forward these two to the PI. The allocation of clusters to either community-based or health facility-based intervention will occur at a public event prior to the trial. Village elders for 3 matched clusters will be asked to draw one opaque sealed envelope each from a box. Each envelope will contain the allocation. The allocation will be immediately recorded and sent to the study statistician, who in turn will provide the DSMB

statistician with a signed, dated copy in a sealed envelope with carbon paper inside to transfer hand written information onto the list inside the envelopes to create an audit trail.

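### An undefined exclusion for suspected non-compliance sits close to the primary outcome and can be applied by staff who know the village's arm

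*Protocol*

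**What the plan says.** Section 8.7.4.4 lists "Suspected non-compliance with the follow-up schedule" twice among the enrolment exclusions, as items 8 and 10. Section 4.1 repeats it as item 10, applied at discharge. Neither place gives a definition, a threshold or an assessor. Section 8.7.2 says "Pre-study screening will be done by hospital staff or study staff".

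The primary outcome in 7.3.1 opens "100% of PMC drugs uptake (defined as administration of" and requires every 3-day course at 2, 6 and 10 weeks. Section 8.9.1 adds that the spot-check questionnaire is meant "to determine if and when children and their mothers/guardians attend the scheduled dosing of the drug".

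Section 4.1 states "Masking: open-label". Section 8.12.3.3 ties arm to village: "Study participants will be randomised to study arms depending on the cluster from which they come from". The protocol then gives two accounts of when the allocation becomes known:

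- Section 11.7.2: "The allocation of clusters to either community-based or health facility-based intervention will occur at a public event prior to the trial".
- Section 8.7.4.2, on the procedure at discharge: "Randomisation will be done by opening a single concealed envelope, which will contain the cluster and study arm". Section 8.7.4 likewise places randomisation after consent.

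**The concern.** A staff member's opinion about whether a family will comply decides who enters a trial whose endpoint is whether the family completes the drug courses. If that opinion can be formed with the arm in view, recruitment can differ between arms after the villages have been randomised. Village randomisation does not protect against that.

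The criterion may also carry a different meaning by arm. Under section 8.1, mothers in the two outpatient (OPD) arms must come back for each course, while mothers in the three take-home arms receive everything at discharge. A family living far away could look doubtful in an OPD village and acceptable in a take-home village. Screening such families out of the OPD arms would raise measured OPD uptake and could hide an advantage of take-home delivery or create an apparent OPD advantage.

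Even if used alike in all arms, the rule may leave a more compliant group than a health system would meet. That matters because the stated purpose is to inform policy on delivery.

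**Working it through.** **Can staff know the arm?**

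- Under 11.7.2, allocation is public before recruitment. At least the delivery mode can then be known for every child once the village is known, and staff must establish residence in order to apply the catchment-area exclusion.
- Under 8.7.4 and 8.7.4.2, the envelope is opened after consent. The village is still the unit, so its arm can be known once its first child has been allocated. Section 8.3 plans 125 clusters and 375 children: 375 − 125 = 250 children (67%) come after a first child. With the 90 villages of sections 8.2 and 8.7.4.2, and 375 children, it is 375 − 90 = 285 (76%). Both counts assume that every village enrols at least one child.

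**Do the stated safeguards cover this?** Block randomisation (11.7.3) balances villages, not the later choice of children within them. The logs (8.7.2, 8.7.3.2) are meant to show unbiased selection, but no reason for exclusion and no count by arm is required. No section keeps the arm from the person judging eligibility.

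**Reproducing the planned design (8.3).** Inputs: 75 children per arm, mean cluster size 3, SD 0.58, ICC 0.1, 10% loss, uptake 50% against 75%, α = 0.05 (taken as two-sided; the protocol does not say).

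- CV² = (0.58/3)² = 0.037
- Design effect = 1 + [(1 + 0.037) × 3 − 1] × 0.1 = 1.21
- Effective n per arm = 75 × 0.9 / 1.211 = 55.7
- Power = 78.6%, against the stated 80%. The unpooled sample-size formula gives 54.9 × 1.211 / 0.9 = 74 per arm, against 75. The design reproduces.

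**Illustration.** The documents give no exclusion rate, so the shares below are assumptions. Let true uptake be 50% in both arms, and let staff remove a share q of would-be non-compliers from one arm only, with no compliers removed by mistake. Observed uptake in that arm is 0.5 / (1 − 0.5q). The standard error of the difference is √(2 × 0.25 / 55.7) = 0.0947.

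| q | Share of all eligible children removed | Observed uptake | False difference | Type I error |
|---|---|---|---|---|
| 10% | 5% | 52.6% | 2.6 points | 5.9% |
| 20% | 10% | 55.6% | 5.6 points | 9.0% |
| 30% | 15% | 58.8% | 8.8 points | 15.4% |

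- Imperfect judgement shrinks this. If 10% of eligible children are removed and 25% of them would have complied, the arm shows (0.50 − 0.10 × 0.25) / 0.90 = 52.8%, with type I error 6.0%. If the excluded children would have complied at the same 50% as everyone else, there is no shift.
- The opposite direction is also possible. With a true 50% against 75%, removing 20% of would-be non-compliers from the lower arm only gives 55.6% against 75%, a difference of 19.4 points, and power falls from 78.6% to 58%.
- If q is the same in both arms and there is no true difference, no false difference arises, but both arms show 52.6% to 58.8% instead of 50%.

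**The case against.** **Order of allocation.** Sections 8.7.4 and 8.7.4.2 put randomisation after consent, by concealed envelope. Section 8.7.6.1 speaks of discharge after randomisation, and exclusion item 3 in 8.7.4.4 refers to the day of randomisation. Section 11.7.2 may be older text: it allocates only between community and facility delivery, and it follows a four-arm description in 11.7.1. A reader might infer from 11.7.2 that staff know the arm for every child. The documents do not settle that. What stands is that staff can know it, for all children on one account and for those after a village's first on the other.

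**Meaning of the criterion.** A reader might infer that in the OPD arms the follow-up schedule is the drug-collection schedule. No section says so. The Table 2 notes and section 8.12.1 describe home visits to check uptake and one closing clinic visit, alike in all arms, and 8.12.4 makes the uptake checks unannounced. Table 2 does place the treatment visits at home or OPD, so the term is ambiguous. A stricter reading in the OPD arms is possible, not established.

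**Repair by analysis.** A reader might infer that no adjustment could help. That goes too far: household GPS (8.7.4.5) and socioeconomic features (8.5) are collected, and 11.7.4 plans adjustment for baseline prognostic factors. Selection acting through distance or wealth could be partly corrected; selection on staff impressions that are not recorded could not.

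**Size.** The illustration assumes perfectly predictive exclusion in one arm, and at 10% the effect is trivial. The power statement in 8.3 concerns SMS support, where distance to the OPD gives no reason for a difference within one delivery mode. Both points stand. However, 8.3 also compares each arm with Arm 1, which includes OPD against take-home at 75 per arm, so the effective sample size used above is relevant there.

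**Conclusion.** The point holds as a recruitment-bias risk built into the enrolment rules. An undefined, subjective criterion closely related to the primary outcome can be applied in an open-label trial by staff who can know the arm under either account of allocation. If it is used differently by arm it can create or mask a difference; if used alike it may raise uptake in all arms and limit generalisability.

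Direction and size are unknown. The range of 52.6% to 58.8% observed uptake, with type I error of about 6% to 15%, rests on assumed one-arm removal of 10% to 30% of would-be non-compliers, perfect prediction, 50% true uptake and a two-sided test. It shows what could happen at this sample size; it is not an estimate. Because this is an enrolment rule, an analysis plan could lessen the problem but not remove it. The change is worth making chiefly because it is cheap.

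**What to change.** - Delete the criterion from 4.1 (item 10) and 8.7.4.4 (items 8 and 10). Rely on the residence and planned-absence rules already present in 4.1 (item 3), 8.7.4.4 (item 5) and 8.7.6.2. Their time limits differ (three weeks in 4.1, one month in 8.7.6.2) and should be aligned at the same time.
- State that eligibility, consent and issue of the study number are completed before anyone consults the village's arm.
- Reconcile 8.7.4.2 with 11.7.2 on how villages are allocated and when the result becomes known.
- In the existing screening logs, record the reason for each exclusion and a village code (the logs may not hold identifying information). Report screened, excluded and refused counts by arm.

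The cost is amendment wording and one or two extra log fields; no visit and no sample-size figure changes. The downside is possibly slightly more loss to follow-up. Section 8.3 allows 10%, but that figure was set with the criterion in place, so whether it absorbs the increase is not shown and should be watched during recruitment.
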